### Outcomes measurement

Primary outcome: Total consumption of sufentanil within 24 h after surgery.

Secondary outcomes:
Assessment of postoperative pain scores at 1, 2, 4, 24, and 48 h after surgery: children aged 1–6 years: due to the special characteristics of children after neurosurgery and of preschoolers who cannot properly express their pain with language, two different scoring methods will be used—the FLACC scale and the FACES facial pain score. Children aged 7–12 years can use NRS for self-assessment in addition to the above two methods.Total consumption of sufentanil within 1, 2, 4, and 48 h after surgery and emergency-remedy medicine consumption at 1, 2, 4, 24, and 48 h after surgery.Postoperative safety indicators: complications including agitation, postoperative nausea and vomiting (PONV), bleeding, infection, hypoxemia, respiratory depression, neurological impairment at 1, 2, 4, 24, and 48 h after surgery, and serious adverse events including disability and death.Length of hospitalization after the surgery.

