### Data collection and management

Investigators will explain the benefits of participating in the trial to patients and their authorized surrogates before surgery. After the operation, a specific blinded investigator will conduct follow-up in the ward at 1, 2, 4, 24, and 48 h. Participants who are unable to complete the assessment of the primary outcome will be excluded in situations such as death or discharge in 24 h. Cases with other deviations and deficiencies except for the aforementioned conditions will be retained. Outcome investigators will receive training on all outcome measures. Nurses, children, and their authorized surrogates will be trained to use the electronic analgesia pump. All electronic analgesia pumps will be calibrated by a researcher according to uniform standards. The anesthesiologists in charge will record the patients’ intraoperative data. The relevant data of the electronic analgesia pumps will be recorded by an electronic memory system. The data are accessible to investigators who are blinded to the trial. A blinded investigator will collect other data on secondary outcomes, such as pain scores, postoperative complications, and length of hospitalization after surgery. The data managers will use double data entry to enter data into the EpiData database. An inspector will examine the data, create records, and revise these records as necessary.

Each participant will have a unique study identifier, and their data will be recorded by an independent data manager. The data will be electronically stored in the EpiData database and undisclosed to other researchers until the study is completed. The final dataset will be handed over to statistical analysts for statistical analysis. Regular data checks and double data entry will be applied to promote data quality.

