### Statistical analysis

Statistical analyses will be performed using SPSS 23.0 software. All measured data will be reported as the mean ± standard deviation ($$ \overline{x} $$ ± s), interquartile range (IQR, 25–75% percentile), or number (%). For normally distributed and equal-variance data, statistical analyses of categorical variables will be carried out using the *t* test or analysis of variance (ANOVA). For abnormally distributed and unequal variance data, statistical analyses of categorical variables will be carried out using a nonparametric test as appropriate. A chi-square test and Fisher’s exact test will be used to compare proportions. For the primary outcome, we will first use ANOVA to compare whether there are differences among the three groups. If there are differences, further multiple comparisons will be performed. The results of the FLACC scores, FACES scores, and NRS scores will be analyzed by repeated measurements for general linear models and multivariate analysis. We will also perform the subgroup analysis based on different ages. We will exclude patients who reject the intervention and whose primary data are missing. Statistical significance will be defined as a *P* value < 0.05.

All randomized participants with informed consent will be analyzed. If unintended missing data related to the primary outcome account for more than 10%, this will be handled with multiple imputation. Analyses will be performed according to the intention-to-treat principle.

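### The pain-score method named for SPSS drops, scale by scale, any child with one missing score, which fits poorly with the promise to analyze all randomized children

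*Protocol article*

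**What the plan says.** The Outcomes measurement section lists among the secondary outcomes "Assessment of postoperative pain scores at 1, 2, 4, 24, and 48 h after surgery". FLACC and FACES apply to all children. NRS self-report is added for ages 7–12.

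The Statistical analysis section names the software, "Statistical analyses will be performed using SPSS 23.0 software", and the method: the three sets of scores "will be analyzed by repeated measurements for general linear models and multivariate analysis".

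Three statements bear on who is analyzed:

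- Statistical analysis: "All randomized participants with informed consent will be analyzed".
- Statistical analysis: "Analyses will be performed according to the intention-to-treat principle".
- Data collection and management, after excluding children whose primary outcome cannot be assessed: "Cases with other deviations and deficiencies except for the aforementioned conditions will be retained".

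The one missing-data rule is limited to the primary outcome: "If unintended missing data related to the primary outcome account for more than 10%, this will be handled with multiple imputation".

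**The concern.** The repeated-measures general linear model in SPSS holds one row per child, with the five time points as five columns. If any of the five is empty, the row is deleted. A child with four observed scores and one gap contributes nothing to that scale's analysis. The article does not say this; it is how the named procedure works, whether its univariate or multivariate tests are read.

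Such a child is an incomplete case of the kind the plan says it will keep, and no stated rule fills the gap. Lower pain scores are part of the hypothesis in the Discussion section. At stake are precision and, if gaps are related to the child's condition, some bias in the group comparison. That relation is most plausible for NRS, because a child has to be able to report. The Anesthesia and analgesia section itself expects that some children aged 7–12 will at first be unable to work the pump button.

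**Working it through.** **Inputs from the protocol.** Five assessments (Outcomes measurement); 54 evaluable and 60 enrolled per group, 180 in total, with 10% loss to follow-up (Sample size).

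**Assumed.** A missing rate m per assessment, independent across the five times. The documents give none.

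**The plan's own figure.** 54 / (1 − 0.10) = 60 per group, and 3 × 60 = 180. It reproduces.

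**Share deleted, per scale.** A child stays only if all five scores are present, so the share deleted is 1 − (1 − m)^5.

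| m (assumed) | Share kept | Share deleted | Kept of 60 per group | Kept of 180 |
|---|---|---|---|---|
| 2% | 0.98^5 = 0.904 | 9.6% | 54.2 | 162.7 |
| 3% | 0.97^5 = 0.859 | 14.1% | 51.5 | 154.6 |
| 5% | 0.95^5 = 0.774 | 22.6% | 46.4 | 139.3 |

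The last two columns apply to FLACC and FACES only. For NRS the percentages hold, but the counts cannot be given because the size of the 7–12 stratum is not stated.

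As a yardstick, 2% per assessment already uses up the 10% allowance (54.2 of 60). That allowance was set for the primary outcome, so this shows scale and is not a breach of the sample size.

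**How far independence matters.** If the same children miss all five scores, the share deleted falls to m itself: 2%, 3% or 5%. If no child has more than one gap, it is 5m: 10%, 15% or 25%. The independent case lies close to the upper end. Gaps in sick or sleepy children tend to cluster, so the true loss at a given m would probably be lower than the table shows.

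**Effect on the estimate.** An illustrative simulation used two arms of 54, a true difference of −0.60 on a standardized scale, and 300 runs (all assumed).

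- 5% of scores missing completely at random: 78% of children complete. The empirical standard error was 0.233 for complete cases and 0.201 for a mixed model, a ratio of 0.233 / 0.201 = 1.16.
- Dropout depending on the previous score: 79% complete. The mean estimate was −0.54 for complete cases and −0.58 for the mixed model. The complete-case shift is 0.06, or 0.06 / 0.60 = 10% of the true difference.

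The precision loss is visible. The bias is small in this setting and depends on the mechanism assumed.

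**The case against.** The strongest reply is that the text is one loosely worded sentence in an article that condenses a fuller protocol. Imputation of secondary outcomes, covariates and covariance structure are commonly left to the full protocol or the analysis plan. That stands for the covariates: the absence of the age stratum or of the day-0 score from the sentence is not an error. It does not remove the point about the method, because the method and software are stated and the stated method has this property.

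A reader might infer that the protocol contradicts its intention-to-treat promise outright. The documents do not support that. Nowhere do they say that a child with a missing pain score will be dropped; the conflict follows from how the procedure works when no imputation is added. A separate sentence in the same section, "We will exclude patients who reject the intervention and whose primary data are missing", is a more direct conflict with intention-to-treat, and this point should not borrow weight from it.

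A reader might also infer that the pain results would rest on the best-recovering children. That is unsupported for FLACC and FACES. The Background calls both scales easy for observers to obtain, and a trained blinded investigator is to visit at every time point, so drowsiness need not prevent a rating. For NRS the worry is reasonable, but it concerns only ages 7–12, and a missing NRS leaves the child's FLACC and FACES intact. Nor does the protocol rank pain scores as the main secondary result; they are one of several.

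Finally, a mixed model is not the only remedy. Multiple imputation of the pain scores would also keep these children in the analysis.

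**Conclusion.** The concern holds as a limited one about secondary outcomes. For each scale, the stated procedure deletes any child with an incomplete set of five scores, and this fits poorly with the statements that all randomized children will be analyzed and incomplete cases retained. The size is conditional: about 10%, 14% or 23% of children per scale at an assumed 2%, 3% or 5% missing per assessment, independent across times, and less if gaps cluster. It rests on reading the sentence as the SPSS repeated-measures general linear model, and on no imputation being added elsewhere. The primary outcome, analyzed by ANOVA at 24 h, is not affected. The change is worth making because it is cheap, not because a large bias has been shown.

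**What to change.** Replace the repeated-measures/multivariate general linear model with a linear mixed model (the MIXED procedure in SPSS), fitted separately for each scale:

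- Fixed effects: group, time as a category, and group by time. For FLACC and FACES add the age stratum used in randomization; NRS lies within one stratum and does not need it.
- Unstructured within-child covariance over the five times.
- All observed scores used, so that a child with at least one score contributes.
- Group differences with 95% confidence intervals at each time.

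The day-0 score in Table 1 may be added as a covariate only if a missing baseline does not remove the child; otherwise the deletion returns by another route.

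The model assumes missing at random. If the child's state itself drives the gaps, it reduces bias but may not remove it. Prespecify a simple sensitivity analysis, for example one that shifts imputed values for missing scores by a range of amounts, with most attention to NRS, and report the number of observed scores by group and time.

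The cost is a change of wording in the analysis plan. The data and the software stay the same.

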### Criteria for discontinuing or modifying the allocated interventions

There will be no special criteria for modifying allocated interventions, but there are conditions under which to terminate the study: (1) unexpected postoperative continuation of intubation; (2) serious adverse events during the operation, such as acute massive hemorrhage, malignant fever, and shock; (3) unplanned reoperation within 24 h after surgery; (4) serious, adverse surgically related events/reactions occurring within 24 h after the operation, such as postcraniotomy hematoma, unconsciousness, coma, and cardiac arrest; and (5) serious adverse events/reactions related to the medicines in electronic analgesia pumps within 24 h after surgery.

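### The primary analysis is labelled intention-to-treat on all randomized children, but other sentences remove randomized children for events after randomization, and the missing-data rules overlap

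*Protocol article*

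**What the plan says.** Two paragraphs of the Statistical analysis section bear on who is analyzed. The first ends with an exclusion: "We will exclude patients who reject the intervention and whose primary data are missing". The second says "All randomized participants with informed consent will be analyzed", then "If unintended missing data related to the primary outcome account for more than 10%, this will be handled with multiple imputation", then "Analyses will be performed according to the intention-to-treat principle".

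Data collection and management adds its own exclusion: "Participants who are unable to complete the assessment of the primary outcome will be excluded in situations such as death or discharge in 24 h". It continues: "Cases with other deviations and deficiencies except for the aforementioned conditions will be retained".

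Two other places bear on the same question without settling it. Eligibility lists failure to wean from intubation after surgery as an exclusion criterion, although Table 1 puts randomization before surgery. The section on discontinuing or modifying interventions says "there are conditions under which to terminate the study: (1) unexpected postoperative continuation of intubation", and goes on to list serious intraoperative events, reoperation within 24 h, and serious surgical or pump-drug events within 24 h. Neither place says whether such a child stays in the analysis.

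**The concern.** A child who is randomized with consent and then refuses the block belongs in the analysis under one sentence and may be removed under another. A child without a 24 h sufentanil total is excluded by one sentence and is a candidate for imputation under another. A child who dies or is discharged within 24 h is excluded in one section and covered by the all-randomized promise in the other.

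At stake is the protection that randomization gives the primary comparison. Refusal, death, early discharge, reoperation and failed weaning all occur after allocation. If their frequency, or the consumption of the children concerned, differs between groups, removing those children distorts the comparison. One listed termination condition concerns serious reactions to the drugs in the analgesia pump. The pump contains sufentanil, whose consumption is the outcome, so a link between loss and outcome is at least possible. With the set not fixed, different analysts could reach different primary populations from the same protocol.

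**Working it through.** **The rules side by side**

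| Child, randomized with consent | All-randomized and intention-to-treat sentences | Exclusion sentences | Imputation sentence |
|---|---|---|---|
| Refuses the block, 24 h data present | analyzed | excluded, if either condition suffices | not needed |
| Accepts the block, 24 h total missing | analyzed | excluded, if either condition suffices | imputed only if over 10% missing |
| Refuses and 24 h total missing | analyzed | excluded on any reading | imputed only if over 10% missing |
| Dies or is discharged within 24 h | analyzed | excluded (Data collection and management) | unclear, since unintended is not defined |
| Fails weaning, or meets a termination condition | analyzed | not stated | not stated |

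The first four rows conflict on at least one reading. The fifth is open.

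**The 10% switch.** 10% of 180 is 18. With 18 missing, imputation does not apply; with 19 it does. The Sample size section plans for 10% loss: 54/(1 − 0.10) = 60 per group, 180 in total, which reproduces the stated figure. The loss planned for therefore sits on the switch point. If 18 were lost evenly, 162 would remain, 54 per group, which is the planned evaluable number. The issue is therefore bias and an undefined set, not a shortfall in planned power.

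**Illustration of size.**

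Inputs from the Sample size section: 54 per group, two-sided alpha 0.017, 80% power, 20% reduction. No mean or SD is given, so the 54 itself cannot be reproduced. Solving the two-sample t test backwards gives a standardized difference of 0.630. The implied SD is 0.20/0.630 = 0.318 of the control mean, a coefficient of variation of about 0.32.

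Assumptions, not in the documents: a fraction f = 0.10 of controls is lost, these children average k times the control mean, and no such loss occurs in the block arm.

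- Observed control mean m = (1 − f·k)/(1 − f).
- Apparent reduction = 1 − 0.80/m.
- Power comes from the noncentral t with noncentrality (m − 0.80)/0.318 × √(54/2) and 106 degrees of freedom.

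| k | m | Apparent reduction | Difference in means | Noncentrality | Power |
|---|---|---|---|---|---|
| no loss | 1.000 | 20% | 0.200 | 3.27 | 80% |
| 1.3 | 0.87/0.90 = 0.967 | 17.2% | 0.167 | 2.73 | 62% |
| 1.5 | 0.85/0.90 = 0.944 | 15.3% | 0.144 | 2.36 | 48% |

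**Limits on k.** For normal data with this SD, the highest 10% average about 1.56 times the mean, so k = 1.5 is close to losing exactly the top consumers. For any distribution, 10% of children can average at most 1 + 0.318 × √(0.9/0.1) = 1.95 times the mean, so ratios of 2 or more are impossible with these inputs.

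**Other direction.** With no true effect and the same loss (10%, k = 1.5) in one block arm only, the spurious difference is 1 − 0.944 = 0.056. The rejection rate for that comparison rises from 1.7% to about 6.9%.

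**Balanced loss.** With the same f and k in both arms, the apparent reduction is 1 − 0.80m/m = 20%, unchanged.

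**The case against.** Much of the text can be read as one scheme: death or discharge within 24 h is a named exclusion, other deviations are retained, and unintended gaps are imputed above 10%. The exclusion sentence may also require both refusal and missing data. This narrows the conflict and shows that the rules are not wholly irreconcilable. It does not remove the conflict. Even the joint reading drops randomized children, refusing a block is not withdrawing consent, and deaths and early discharges still leave a set described as all randomized.

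A reader might infer that the 10% trigger lets the analyst choose the estimand after seeing the data. The documents do not support that, because the threshold is mechanical and stated in advance. The weakness is that it sits beside a sentence excluding the same missing cases and switches method at the planned loss.

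A reader might also infer that data will be lost mainly in sick or poorly controlled children. The protocol does not say so. Poor pain control leads to remedial analgesia, not to loss of data, and pump use is held in electronic memory. Outcome observers and patients are to be blinded, which limits group-related refusal. Some termination events, such as coma, could go with low consumption and reverse the direction of bias.

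The illustration is also pessimistic in its details. It holds the SD fixed and sets the block arm at 54, although only controls are lost. If the block arm keeps 60 and every lost control sits exactly at k, the remaining control variance is [(1 + 0.318²) − 0.1k²]/0.9 − m². The control SD is then 0.318 at k = 1.3 and 0.285 at k = 1.5, and power is about 65% and 55%. The contradiction does not depend on any of these figures.

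**Conclusion.** The point holds as a contradiction in the current text, not as detail left to an analysis plan: the article states these rules, and they do not define a single primary analysis set. Followed literally, children can be removed for post-randomization reasons from an analysis labelled intention-to-treat.

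The bias could run either way, and its size is unknown. The figures of 17% to 15% apparent reduction and 62% to 48% power show only what one-sided loss of high consumers could do. They rest on 10% loss in the control arm alone, ratios of 1.3 to 1.5, the back-solved coefficient of variation of 0.32, 54 per group and a fixed SD. Loss of the same kind in both arms would leave the 20% reduction intact. The passages should be reconciled before the blind is broken.

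**What to change.** 1. Define one primary set: every randomized child with consent, analyzed in the allocated group whatever block was received. Use stored pump data wherever the full 24 h was observed.
2. Delete the exclusion sentence in Statistical analysis and the death or discharge exclusion in Data collection and management.
3. State that the weaning criterion in Eligibility and the listed termination conditions, when they occur after randomization, do not remove a child from this set. This concerns the analysis only; the clinical conditions themselves are not at issue.
4. Use one missing-data rule in place of both the complete-case exclusion and the 10% switch, for example multiple imputation using group, age stratum, earlier consumption and pain scores.
5. Treat consumption cut short by death, early discharge or termination as incomplete. Totalling the pump record only up to the event would score such a child as a low consumer, and so as an analgesic success. State the handling in advance and add a sensitivity analysis.
6. Report complete-case and per-protocol results only as labelled sensitivity analyses.

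The cost is a few sentences of text and slightly more analysis work. No new data collection is needed, since pump use is already recorded electronically.

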### Dissemination

The study protocol has been registered and is available on the Chinese Trial Registry website (registered in ChiCTR.org with the identifier ChiCTR1800017386). The results will be disseminated to all participants, researchers, and healthcare providers through study summary documents, courses, presentations, and the Internet. The datasets analyzed during the current study are available from the corresponding author on reasonable request.

## Discussion

All pediatric patients who undergo craniotomy require analgesic medications for postoperative analgesia. SNB is a simple strategy that can relieve postoperative pain. In this trial, we hypothesize that ropivacaine, which is the SNB administered in pediatric patients undergoing neurosurgery, will decrease the requirement for sufentanil and other pain medications as well as reduce postoperative pain scores. The second aim is to determine whether preoperative block or postoperative block is more suitable for postoperative pain control. This study will be a prospective, randomized, controlled, double-blind study. Participants are randomized into three groups: preoperative SNB group, postoperative SNB group, and nonblocking control group, who will be followed for 48 h postoperatively and then the day of discharge. We have set the same standardized anesthesia protocol to avoid sources of bias and will use the FACES facial pain assessment method based on the FLACC scale to improve the accuracy of pain measurement. The study will be carried out at Beijing Tiantan Hospital, Capital Medical University (which has the highest rank for neurosurgery in China). This investigation is a single-center study, which may bias our results. However, the results of this study may promote the development of postoperative analgesia and popularize the optimal pain management of children.

